## Methods

### Study population

The aim is to recruit a population of people with PCD in seven study centers in Germany, all of which are experienced in the care of pwPCD, and with the support of the patient organization “Kartagener Syndrom und Primäre Ciliäre Dyskinesie e.V.” (e.g., from the 2024 PCD Patient Congress).

The participants in the study should be able to perform a PA program safely, to perform the motor tests reliably, and to have a certain level of media literacy and a sufficient attention span to complete the online PA courses. The study centers require a PCD outpatient clinic with physicians experienced in care, the possibility of ECG, and pulmonary function diagnostics.

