### Strategies for recruitment and retention

In the 7 study centers, 280 pwPCD are regularly supervised annually. According to these study centers, 193 of these pwPCD meet the inclusion criteria, so that recruitment of 100 participants is realistically feasible.

Patients will be informed by flyers and posters in their outpatient department. In addition, patients will be recruited through the patient organization “Kartagener Syndrom und Primäre Ciliäre Dyskinesie e.V.” (200 association members with PCD) and the annual patient congress (on average 40–50 participants with PCD in all age groups).

Recruitment procedures will differ between hospitals and the congress setting. Recruitment should fit as well as possible into the respective clinic’s daily routine and the congress program to ensure feasibility and success. The procedure described below will therefore be adapted to the conditions in the respective setting; screening manuals will be written. To allow an analysis of the feasibility of recruitment, numbers (*N*) of patients screened in the different steps shall be documented in a screening log.

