#### General procedure for recruitment via the patient organization

Recruitment as part of the patient congress

With the registration confirmation for the 2024 patient congress in Hamburg, the patient organization will send a reminder for the study. The inclusion and exclusion criteria are again pointed out here and congress participants are asked to bring all medical documents including cilia and genetic findings to the congress, if interested in study participation. This is necessary to be able to decide about eligibility for study participation at the congress. Congress participants who could take part in the study according to the inclusion and exclusion criteria will be informed verbally and in writing. After written information has been provided (see above), the screening visit including the motor test will be carried out on the same or following day. For the follow-up visits, appointments are either made at the lead study center in Bochum or the participants agree to a telephone visit. In this case, an examination close to home, including pulmonary function tests, is required by the treating doctor, for whom a confidentiality agreement must be in place. The following motor tests are carried out close to home after an appointment has been made with the training institute. The rest of the procedure corresponds to that in the study centers (see above).

b)Recruitment via mailing list or homepage

If a pwPCD contacts the central study center Bochum via advertising on the homepage or via the email distribution list of the patient organization, they will receive telephone and written information about the study. The inclusion and exclusion criteria will be checked in a telephone conversation. If participation in the study is not excluded in principle, an appointment will be made in Bochum for the screening visit and the motor test. Both will take part as described above for congress participants.

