#### Adverse events and serious adverse events

In the following, we define the AEs and SAEs to which we are limited in this study due to the chosen intervention and the clinical characteristics of PCD. They comprehensively recognize both the expected risks and serious complications.

Adverse event (AE)Any unplanned doctor contactPulmonary exacerbation or other pulmonary complications (obstruction, etc.)New antibioticsAccident during physical activity without hospital contactMedically justified discontinuation of physical activity (single occurrence)Discontinuation of intervention due to a medical cause

Serious adverse event (SAE)DeathAny unplanned hospitalization or hospital presentation

For adverse events (AEs), the following guidelines will be used to describe severity.Mild—Events require minimal or no treatment and do not interfere with the participant’s daily activities.Moderate—Events result in a low level of inconvenience or concern with therapeutic measures. Moderate events may cause some interference with functioning.Severe—Events interrupt a participant’s usual daily activity and may require systemic drug therapy or other treatment. Severe events are usually potentially life-threatening or incapacitating. Of note, the term “severe” does not necessarily have to be identical with “serious.”

All adverse events (AEs) will have their relationship to study procedures, including the intervention, assessed by appropriately trained clinicians (pediatric and internal medicine) based on temporal relationship and his/her clinical judgment. The degree of certainty about causality will be graded using the categories below.Related—The AE is known to occur with the study procedures, there is a reasonable possibility that the study procedures caused the AE, or there is a temporal relationship between the study procedures and the event. Reasonable possibility means that there is evidence to suggest a causal relationship between the study procedures and the AE.Not related—There is not a reasonable possibility that the study procedures caused the event, there is no temporal relationship between the study procedures and event onset, or an alternate etiology has been established.

During each study visit (V2–V4), a standardized query (CRF) is made by means of questionnaires of the AEs and SAEs defined above. In addition, all participants are encouraged to report unplanned hospitalizations (SAEs) to their supervising study center within 48 h.

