Information to be collected includes event description, time of onset, clinician’s assessment of severity, relationship to study procedures (assessed only by those with the training and authority to make a diagnosis), and time of resolution/stabilization of the event. All AEs occurring while on study will be documented appropriately regardless of relationship. All AEs will be followed to adequate resolution.

All (S)AEs are documented in the central study database by the responsible study center. If an AE or SAE is recorded in the central database, the study team of the lead study center Bochum is automatically informed. In addition, the SAE report can be forwarded to the lead study center via fax. The study team will then contact the registering study center and the subject to obtain further information. In the case of SAEs, the SAE board is immediately involved. The intervention will be interrupted until the final clarification of whether there is a risk for the participant by continuing the intervention. The lead study center in Bochum will inform the participants as soon as possible whether the intervention can be resumed.

The lead study center Bochum will record events with start dates occurring any time after informed consent is obtained until the last day of study participation. The documents are submitted to the DSMB once a year for further review.

The local study management at each site is responsible for truthfully documenting all AEs and SAEs during study visits and for notification also in between in the central database. The lead study center in Bochum and the PI receives an automated notification from the central database upon registration and must check it immediately. SAE reports are forwarded to the SAE board within 72 h. After the final assessment of the event, the documents are collected and forwarded bundled to the DSMB once a year by the PI or a named representative of the leading study center in Bochum. In the event of an accumulation of study-relevant SAEs, early convening of the DSMB and notification to the relevant ethics committee will be made by the PI. The assessment of the event is documented in the central database by the study team at the Bochum University Children’s Hospital.

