As part of the underlying disease, pulmonary exacerbations and associated doctor contacts or unplanned hospital stays are common. If this constellation emerges during the examination by the central study center, it is not necessary to involve the SAE board for verification. The assessment and documentation are then carried out by the study team from Bochum directly in the central database. The DSMB is regularly informed by the annual report. If there is an increase in pulmonary exacerbations in a study center or the study, the PI or a named representative is obliged to inform the SAE board separately within 72 h. Depending on the assessment of the SAE board, an early notification to the DSMB as well as to the ethics committee responsible will also be made by the PI in this case.

After assessing the event, the study team from Bochum will contact the participant by telephone to discuss further procedures regarding the study. If pathological findings are detected during the study visits, the participant will be informed directly orally about the findings and a recommendation for further (subject-specific) clarification will be made. If requested, the participant may be provided with a copy of the examination results for the doctor providing further treatment.

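### Hospital presentations without admission are SAEs by definition, but the 48-hour request leaves them out, and what counts as a hospital presentation is not defined

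*Protocol article*

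**What the plan says.** All of the following is in the protocol article.

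- *Adverse events and serious adverse events*, definitions: unplanned contact with a doctor, in any setting, is on the AE list. The SAE list has two entries, death and any "unplanned hospitalization or hospital presentation". The article says that the trial confines itself to these lists. It does not define a hospital presentation.
- Same section, reporting by participants: a standardized AE and SAE query takes place at V2 to V4. In addition, "all participants are encouraged to report unplanned hospitalizations (SAEs) to their supervising study center within 48 h".
- Same section, consequences: "In the case of SAEs, the SAE board is immediately involved". SAE reports go to that board within 72 hours. For the programme, "The intervention will be interrupted until the final clarification of whether there is a risk for the participant by continuing the intervention". An accumulation of study-relevant SAEs leads to early convening of the DSMB.
- Same section, exemption: where an event proves to be a pulmonary exacerbation with its associated doctor contact or unplanned hospital stay, "it is not necessary to involve the SAE board for verification", and the lead centre assesses it directly.
- *Study population*: "The study centers require a PCD outpatient clinic with physicians experienced in care". *Strategies for recruitment and retention* describes the centre setting as hospitals: "Recruitment procedures will differ between hospitals and the congress setting".
- *General procedure for recruitment via the patient organization*: for participants followed by telephone, "an examination close to home, including pulmonary function tests, is required by the treating doctor".

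**The concern.** The section uses the term SAE with two scopes. The definition includes presentations without admission, and the 48-hour request does not. An emergency attendance that ends with the participant going home falls between them. It is an SAE by definition, but participants are given no reason to report it before the next visit. The board review, the 72-hour forwarding and the interruption can start only once the trial team knows of the event. If it surfaces weeks or months later, these safeguards come too late to serve their purpose.

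The second weakness is the boundary itself. Nothing limits a hospital presentation to admission, an emergency setting or a given seriousness, and nothing excludes outpatient visits. Because the centres see their patients in hospital clinics, an unscheduled visit there fits both lists, while the same complaint taken to a doctor outside a hospital fits only the AE list. The SAE count that feeds the early-DSMB trigger would then partly reflect where participants seek care. In the intervention arm, the classification also decides whether the SAE interruption rule applies.

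**Working it through.** The article gives no event rates, so the check is a comparison of texts plus the visit intervals.

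**1. Scope of the term SAE, sentence by sentence**

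| Place in *Adverse events and serious adverse events* | Hospitalization | Presentation without admission |
|---|---|---|
| SAE definition | yes | yes |
| 48-hour request to participants | yes | not named |
| Exacerbation exemption from the SAE board | yes (hospital stays) | not named, except as a doctor contact |

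Only the definition names the presentation without admission.

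**2. How late such an event could surface**

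V2, V3 and V4 are at 3, 6 and 12 months (*Outcome and other non-safety assessments*). The nominal gaps between queries are:

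- randomization to V2: 3 − 0 = 3 months
- V2 to V3: 6 − 3 = 3 months
- V3 to V4: 12 − 6 = 6 months

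The ±2-week visit window, and the up to 4 weeks allowed for a visit postponed on medical grounds, can lengthen these. The intervention lasts 6 months, so the interruption rule bears on the first two gaps. The third concerns safety reporting only.

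**3. Other routes of detection**

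- Sites must also notify events between visits, which works if the site knows of the event. A presentation at the study centre is known there. One at another hospital need not be.
- The weekly safety questions in *Safety assessments* go to the intervention group and ask about critical complaints related to activity. No equivalent is stated for controls.

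**4. The boundary between AE and SAE**

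Take an unscheduled visit for a complaint that is not an exacerbation.

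- At a hospital PCD clinic it is an unplanned doctor contact (AE item) and, read literally, an unplanned hospital presentation (SAE item).
- At a practice outside a hospital it is the first only.
- The accident item on the AE list is restricted to cases without hospital contact. The doctor-contact item has no such restriction.

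On the first reading the board and the interruption apply. On the second, neither follows from the event's classification.

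**5. The same visit when it is an exacerbation**

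The exemption removes the SAE board step. It does not say that the event stops being an SAE or that the interruption is lifted. The lead centre then telephones the participant about how to proceed, which suggests that it decides on continuation, but the status of the programme until then is not stated. Separately, *Study intervention discontinuation and participant discontinuation/withdrawal* already requires activity to pause for an acute exacerbation, whatever the event is called. The label therefore changes less here than in step 4.

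**The case against.** The strongest reply is that this is a small wording gap in a deliberately broad safety net. An SAE is ordinarily also an AE, so appearing on both lists is not an error. The accident item suggests that hospital contact was meant as the dividing line, and over-capture is the cautious side to err on. Exacerbations, the commonest reason for such visits in this disease, are exempt from the board. Activity already pauses for a list of symptoms, including infection with a feeling of illness, chest pain and undue breathlessness. Participants are only encouraged to report, while sites carry the duty to notify.

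Most of this stands, and it narrows the point. It does not remove the mismatch: a broad definition catches nothing early if the request for prompt reports is narrower. Nor does it settle non-exacerbation visits to a hospital clinic, which the exemption does not cover.

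A reader might infer more, in four ways that the article does not support:

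- **Biased SAE comparison.** Definitions and the V2 to V4 query are the same in both arms. That only one arm has a programme to interrupt does not bias the counts.
- **A share of participants exposed.** The feasibility figure of 100 recruits from the centres, set against the target of 158, gives 100/158 = 63%. But this is a feasibility statement about recruitment, not about where people go when ill. Centre patients may see local doctors, and organization recruits may be followed in Bochum. The close-to-home examination concerns scheduled follow-up.
- **A count of interruptions.** This needs a rate of unplanned visits, which the article does not give, and would have to exclude visits for which activity pauses anyway.
- **Severity set by place of care.** Mild, moderate and severe are rated separately. Only the serious or non-serious classification is affected.

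**Conclusion.** The point holds in two parts. First, the SAE definition and the 48-hour request contradict each other in scope. Under the text as written, a presentation without admission can remain unknown until the next query, nominally up to 3 months during the intervention and up to 6 months between V3 and V4. This assumes that neither the site nor a weekly contact picks it up sooner. Second, because a hospital presentation is undefined and the centres are hospital clinics, the serious or non-serious status of a non-exacerbation visit can depend on the place of care. The effect is smaller for exacerbations.

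The number of affected events cannot be derived from the article. The consequences lie in safety reporting, in the SAE count behind the early-DSMB trigger, and in when the interruption rule applies. Nothing here calls the primary analysis into question. The correction is worth making because it is specific and nearly free.

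**What to change.** 1. Extend the 48-hour sentence to all SAEs as defined, that is, to unplanned hospitalizations or hospital presentations, and use the same wording in the information given to participants.
2. Reconcile the definitions, the consequences and the exemption within *Adverse events and serious adverse events* on two questions: whether an unscheduled visit to a hospital outpatient clinic is a hospital presentation, and whether the interruption applies to the exacerbation events exempted from the SAE board. Both are clinical rules for the sponsor to decide. The review asks only that each have one stated answer that sites can apply uniformly.

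The cost is a change of wording, a note to sites and a few more prompt reports from participants. Recruitment began in March 2024, so events already entered may need to be checked and recoded once the second item is settled.

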#### Unanticipated problems

This protocol uses the definition of unanticipated problems as defined by the Office for Human Research Protections (OHRP). OHRP considers unanticipated problems involving risks to participants or others to include, in general, any incident, experience, or outcome that is unexpected in terms of nature, severity, or frequency. That furthermore is elated or possibly related to participation in the research and suggests that the research places participants or others at a greater risk of harm (including physical, psychological, economic, or social harm) than was previously known or recognized. All serious medical unanticipated problems are captured by the AE and SAE notifications and reported accordingly. All other unanticipated problems are documented. Participants will be informed about UPs on an individual or aggregate level as appropriate.

#### Participant timeline

See Fig. 2.

**Fig. 2 Fig2:**
[figure not shown]
Timeline for participants

#### Sample size determination

For the physical domain of the QoL-PCD 15.2 points were proposed as minimum clinically significant change, the observed standard deviation (sd) in a similar patient group was 30.4 [38]. Sample size calculation for a two-sided two-sample *t*-test at a significance level (*α*) of 5% resulted in a required sample size of 64 per group to reach a power of approximately 80% to detect an effect size of 0.5 (15.2/30.4). Assuming a drop-out rate of 5%, 158 participants should be recruited.

PCD is a rare disease for which there are few specialists. Medical research in PCD and especially in therapy has made little progress to date. Many pwPCDs therefore have a great interest in clinical research and a close bond with their practitioners and travel long distances to do so. We can therefore expect a high level of compliance.

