#### Measures to minimize bias: randomization and blinding

To guarantee adequate sequence generation and allocation concealment, centralized online randomization with 1:1 allocation to intervention or control group is done through REDCap. A person at the AMIB not further involved in the study creates randomization lists based on permuted blocks of random length and are stratified by age group (6–12, 13–17, ≥ 18 years) and FEV1 (≤ / > 60%) to guarantee nearly equal group sizes within the strata. Allocation concealment will be ensured, as the service will not release the randomization code until the patient has been entered into the trial, which takes place after all baseline measurements have been completed.

It is not feasible nor possible for the participating patients and most project staff to be blinded to treatment allocation. Primary outcome assessment will be based on patient reports. Staff who analyze the data will be blinded (arms will be designated randomly at that point as A and B). Data review will be performed blinded.

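### The recruitment target of 158 does not follow from 64 per group with 5% drop-out, which gives 135 (136 with equal arms)

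*Protocol article*

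**What the plan says.** The protocol article, section *Sample size determination*, gives all the inputs in one paragraph:

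- Target difference: "For the physical domain of the QoL-PCD 15.2 points were proposed as minimum clinically significant change".
- Variability: "the observed standard deviation (sd) in a similar patient group was 30.4".
- Test: "Sample size calculation for a two-sided two-sample *t*-test at a significance level (*α*) of 5" per cent.
- Result: the calculation "resulted in a required sample size of 64 per group to reach a power of approximately 80" per cent, "to detect an effect size of 0.5 (15.2/30.4").
- Recruitment: "Assuming a drop-out rate of 5%, 158 participants should be recruited".

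The section on randomization and blinding specifies "centralized online randomization with 1:1 allocation to intervention or control group". The Abstract repeats 158 as the number to be included.

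The section *Strategies for recruitment and retention* starts from 280 patients supervised at the seven centres and says that "193 of these pwPCD meet the inclusion criteria, so that recruitment of 100 participants is realistically feasible". It then names a further source: the patient organization, with 200 members who have PCD, and its annual congress, with 40 to 50 participants who have PCD. It gives no expected yield for that source and does not mention 158.

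**The concern.** The paragraph is laid out as a complete derivation, and its last figure cannot be obtained from the ones before it. This differs from a detail left to the full protocol or the analysis plan: the inputs and the result are both printed, and they disagree.

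The number itself is not in doubt, since 158 appears consistently. Its justification is. That affects two decisions:

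- **Judging a shortfall.** Poor recruitment is listed as a possible ground for suspending or ending the study, and recruitment has an expected end date. If between 136 and 157 participants had been recruited by then, the stated assumptions would call the trial full size, while the stated target would call it short. In a rare disease with a limited pool of eligible people, 22 participants matter.
- **Reading the result.** Anyone interpreting a null finding needs to know whether the design aimed at about 80% power with a large allowance for loss, or at about 86% with a small one.

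**Working it through.** **Inputs** (all from *Sample size determination*, except the allocation ratio, which is from the randomization section): difference 15.2 points; SD 30.4; two-sided two-sample t-test; alpha 0.05; 64 per group; power about 80%; drop-out 5%; target 158; allocation 1:1.

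**Step 1. Reproduce the 64 per group.**

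Effect size d = 15.2/30.4 = 0.5. Power is the probability that a noncentral t variable with 2n − 2 degrees of freedom and noncentrality d × √(n/2) exceeds the two-sided 5% critical value in absolute size.

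- Solving for 80% power gives n = 63.8, rounded up to 64 per group.
- At n = 64 the noncentrality is 0.5 × √32 = 2.83 and power is 80.1%.

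This agrees with the plan. The number of evaluable participants is 2 × 64 = 128.

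**Step 2. Apply the stated 5% drop-out.**

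- N = 128/(1 − 0.05) = 134.7, so 135.
- Rounding per arm: 64/0.95 = 67.4, so 68 per arm, 136 in total.
- The cruder mark-up gives the same: 128 × 1.05 = 134.4, so 135.

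The plan states 158. The excess is 158 − 136 = 22 (22/136 = 16%), or 23 against 135. Rounding cannot explain it.

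**Step 3. What would give 158?**

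- Implied drop-out: 1 − 128/158 = 30/158 = 19.0%.
- Required total at other drop-out rates:

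| Drop-out | 128/(1 − rate), rounded up | Equal arms |
|---|---|---|
| 5% | 135 | 136 |
| 10% | 143 | 144 |
| 15% | 151 | 152 |
| 20% | 160 | 160 |

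- A higher design power, keeping 5% drop-out: 85% power needs 73 per group, and 146/0.95 = 153.7, so 154. For 90% power, 86 per group are needed and the total is 182. Neither gives 158.

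**Step 4. What does 158 deliver under the stated assumptions?**

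- Evaluable: 158 × 0.95 = 150.1, about 75 per group.
- Noncentrality at n = 75: 0.5 × √37.5 = 3.06; power 86.0%.
- With no loss (79 per group): 87.8%.
- For comparison, 136 with no loss (68 per group): 82.5%.
- 80% power is kept as long as 128 remain evaluable, that is, up to a loss of 30 of 158 (19%).

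**The case against.** **A step may have been lost when the article was condensed.** This is the strongest reply, and it stands in part. One route can be constructed. It assumes an allowance for a rank test, which appears nowhere in the document: dividing 64 by 0.864, the lower bound of that test's relative efficiency, gives 74.07, so 75 per group, and 150/0.95 = 157.9, so 158. In that case 64, 5% and 158 would all be intended. It cannot be shown that this was done: the paragraph names a t-test, and the primary analysis is a linear model. The possibility does mean that one should not conclude that one of the three figures must be wrong. Either a figure is wrong or a step is missing, and in both cases the paragraph needs correcting.

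**The error is harmless.** For power this is right. At 158 the trial exceeds its stated power on its own assumptions.

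Two stronger readings are tempting, and the document does not support them.

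- A reader might infer from the recruitment section that only 100 participants can be reached, so that 158 is contradicted and the trial will be underpowered. The 100 is drawn from the 193 eligible patients at the seven centres. The patient-organization route is then added explicitly, and its procedures have a section of their own. The text does not cap recruitment at 100. Nor would a t-test power figure at 100 describe the planned analysis, which adjusts for baseline quality of life.
- A reader might infer that the stated 80% is itself wrong. The document attaches it to 64 per group, where it is correct, and does not claim it for 158 or for 100.

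**Conclusion.** The point holds as an error of derivation in the trial's headline size. From the printed inputs the number to recruit is 135, or 136 with equal arms, and not 158. The 64 per group and its power of about 80% are correct.

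The conclusion rests only on the document's own figures and on reading drop-out in the usual way, as the fraction of recruited participants who are not evaluable. The 86% at 158 with 5% loss is for the stated unadjusted t-test at d = 0.5; the power of the planned covariate-adjusted model is not assessed here.

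The primary inference is not endangered. The paragraph still needs correction, because the stated size of the trial should be reproducible from its stated assumptions.

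**What to change.** Rewrite the sample size paragraph so that its last figure follows from the others. The study team knows which of these applies:

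1. **Keep 158.** State the drop-out rate or the additional inflation step that actually produced it, together with the resulting power: about 86% by the t-test at 5% loss, with 80% retained down to 128 evaluable participants (up to 19% loss). A 19% drop-out assumption should be written in only if it was in fact made, since the same section expects high compliance.
2. **Keep 5% drop-out.** State 136 and change the Abstract to match. As recruitment has begun, the lower target should be documented as a change with its reason.

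In the same revision, add a sentence to *Strategies for recruitment and retention* saying that the 100 refers to the study centres alone and that the rest of the target is to come through the patient organization: 158 − 100 = 58 under option 1, or 136 − 100 = 36 under option 2.

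The cost is a few sentences. Neither option needs more participants than the 158 already planned.
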